### Plans to promote participant retention and complete follow-up {18b}

To minimise participant drop out (and also improve adherence to CGM device use, as new CGMs will be provided at each trial visit), participants will be enrolled in the trial who are already receiving T1D care at the participating clinics, and reminders will be sent to participants before the scheduled visits. In addition, travel reimbursement will be provided for each trial visit to minimise the chance that socio-economic issues may influence participant dropout and adherence to CGM device use. Should a participant miss a trial visit, the sites will attempt to contact them and reschedule the missed visit as soon as possible, as well as counsel the participant on the importance of maintaining the assigned visit and CGM device schedule.

### Data management {19}

The trial sponsor (FIND) will be responsible for the data management, including risk-based monitoring, quality control checks, data cleaning, and protocol compliance. Clinical data and laboratory results will be captured by site staff onto paper-based CRFs during trial visits and entered onto an electronic case report form designed by FIND in the electronic data capture (EDC) system. Site staff will undergo a training session provided by FIND on the use of the EDC system, and will be responsible for entering their data from a paper CRF into the EDC system whenever direct capture into EDC is not possible. The trial Investigators will be responsible for verifying that data entries are accurate and correct, and that data entered in EDC are consistent with the source documents (or the discrepancies adequately explained). Records and documents, including signed informed consent forms, pertaining to the conduct of the trial will be retained by the Investigators for the time mandated by local regulations and institutional policies, and no records may be transferred to another location or party without written permission from FIND.

### Confidentiality {27}

All information obtained will be regarded as strictly confidential and handled and stored according to all relevant Data Protection laws. Only the trial site staff directly involved in the conduct of the trial will be able to identify participants, and any data will be transferred for analysis or published in such a way that participants cannot be identified. Hard copies of all participant records will be kept for 10 years in a locked facility at all sites.

### Plans for collection, laboratory evaluation and storage of biological specimens for genetic or molecular analysis in the trial/future use {33}

No biological specimens will be collected, unless they are collected as part of standard of care at each participating diabetes clinic.

## Statistical methods

### Statistical methods for primary and secondary outcomes {20a}

A separate Statistical Analysis Plan will provide a detailed description of the planned statistical analyses and only a brief outline will be presented here. Please see the ‘Outcomes {12}’ section for definitions of the primary, secondary and exploratory outcomes and for further details on data presentation.

For the purposes of this trial, the following populations will be defined:Enrolled population: all participants enrolled in the trial who completed informed consent.Assigned population: all participants who have been assigned to a trial arm and completed all Day 1 trial visit procedures.Fully Complied: all participants who fully complied with the protocol.Partly Complied: all participants who recorded HbA1c values at Visit 1 and 5 (at least).Intervention: all participants in the CGM device arms who fully complied with the protocol.Safety: all participants who have been assigned to a trial arm.

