### Outcomes {12}

#### Primary outcome

The primary endpoint will be the mean change from baseline (pre-CGM device use) HbA1c at various timepoints up to 15 months (percentage and mmol/mol). This will be assessed in all trial arms and presented as absolute values and percentage changes, together with summary statistics and statistical comparisons (between group).

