#### Exploratory outcomes

In Kenya, the accuracy of the HbA1c point-of-care device used at each participating clinic will be assessed using a laboratory-based HbA1c method as reference. Mean relative bias, 95% limits of agreement and regression estimates will be presented. In South Africa, there are no exploratory outcomes, HbA1c test results analysed for the trial will be the ones used as per routine care.

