**INTERVENTION**							
CGM device application or distribution^b^		Arms 1 and 2	Arm 2	Arm 2	Arm 2	Arm 2	

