**ASSESSMENTS**							
Doctors visit (medical chart review)			All	All	All	All	All
HbA1c assessment			All	All	All	All	All
Medical events and resources survey				All	All	All	All
GMSS		All			All		All
HRQoL assessments		All				All	All
DDS		All			All	All	All
Acceptability questionnaire					Arms 1 and 2		Arms 1 and 2
Focus group discussion^c^						All	

*CGM* Continuous glucose monitoring, *DDS* Diabetes distress score, *GMSS* Glucose Monitoring Satisfaction Survey, *HRQoL* Health Related Quality of Life

^a^Includes identification of potential participants to be invited to the screening and enrolment day

^b^In the continuous CGM arm, the device is applied on on Day 1 and used until Month 9, for the periodic arm, a new device is provided at the visits shown and used for 1 week before each clinic visit (except for the enrolment visit), and for 1 week after each clinic visit (except for the final follow-up visit)

^c^Performed in a subset of participants

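### South Africa's schedule has no HbA1c at Visit 1, which contradicts the pre-CGM baseline and the Partly Complied definition

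*Protocol article*

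**What the plan says.** All references are to the Protocol article.

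- **Endpoint.** Outcomes {12}, Primary outcome, defines the endpoint as "mean change from baseline (pre-CGM device use) HbA1c", followed up to 15 months.
- **South African schedule.** In Table 2 the row "HbA1c assessment" is blank at Day 1 (Visit 1) and marked for all arms at Week 1 (Visit 2) and Months 3, 6, 9 and 15.
- **Start of CGM.** In the same table the row "CGM device application or distribution" marks Arms 1 and 2 at Day 1. The footnote says that the continuous-arm device is applied "on Day 1 and used until Month 9".
- **Kenyan schedule.** Table 1 marks HbA1c at Day 1, leaves Week 1 blank, and then marks Months 3, 6, 9 and 15.
- **Populations.** Statistical methods {20a} defines "Partly Complied: all participants who recorded HbA1c values at Visit 1 and 5 (at least". The primary analysis uses the Fully Complied or Partly Complied population, and hospitalisations use Partly Complied only. Fully Complied rests on full compliance with the protocol and names no visit.
- **Source of South African values.** Under Exploratory outcomes, for South Africa, "HbA1c test results analysed for the trial will be the ones used as per routine care". Eligibility criteria {10} requires an HbA1c of at least 10% within the past 3 months there.

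**The concern.** The article fixes a baseline definition, an assessment schedule and an analysis population, and for South Africa the three do not fit together. This is a conflict between stated rules, not detail left to the analysis plan.

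Whoever analyses the South African data must choose one of three routes: exclude those participants from Partly Complied, use the Week 1 value, or use an earlier routine value. The article does not choose. Three of the six clinics are South African (Study setting {9}), the trial is open-label, and recruitment there has begun (Trial status). A choice made after results are seen would be open to challenge. Baseline could also mean different things in the two countries without anyone having decided that it should.

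**Working it through.** **1. Is the blank cell an extraction fault?** Table 2 has a row label and seven time columns, so eight cells per row. The HbA1c row has eight cells. In the same table GMSS, HRQoL and DDS fall on Day 1, so there is no general column shift.

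| | Day 1 (V1) | Week 1 (V2) | M3 (V3) | M6 (V4) | M9 (V5) | M15 (V6) |
|---|---|---|---|---|---|---|
| HbA1c, Kenya | yes | – | yes | yes | yes | yes |
| HbA1c, South Africa | – | yes | yes | yes | yes | yes |
| CGM given, South Africa | Arms 1, 2 | Arm 2 | Arm 2 | Arm 2 | Arm 2 | – |

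**2. Against the endpoint.** Baseline must precede CGM use. The first scheduled South African HbA1c comes about a week after CGM starts in Arms 1 and 2. In Arm 3 the Week 1 value is post-randomisation but not post-CGM.

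**3. Against the populations.** Partly Complied needs HbA1c at Visits 1 and 5. Table 2 schedules Visits 2, 3, 4, 5 and 6. Someone who follows it exactly meets Fully Complied but has no scheduled Visit 1 value, so the stricter population is no longer contained in the looser one.

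**4. The plan's own sample size.** Inputs from Sample size {14}: effect size 0.2, three arms, 5% significance, 80% power, N = 246. Reading 0.2 as Cohen's f in a one-way ANOVA:

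- λ = N·f², with k − 1 = 2 and N − k degrees of freedom
- power = P(F′(2, N − 3, λ) > F critical value at 5%)
- N = 246: λ = 246 × 0.04 = 9.84, power 80.4%
- N = 243: power 79.8%

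So 246 is the smallest balanced total that reaches 80%, and the stated figure reproduces.

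**5. Illustration of a literal exclusion.** The article gives no country split and does not say whether 246 is the total or per country. Assume that it is the total, that South Africa supplies the share shown, and that all South African participants are excluded:

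| South African share (assumed) | N left | λ = N × 0.04 | Power at f = 0.2 |
|---|---|---|---|
| 1/3 | 164 | 6.56 | 62% |
| 1/2 | 123 | 4.92 | 49% |
| 2/3 | 82 | 3.28 | 34% |

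If 246 is instead per country, the same literal reading leaves no South African participant in Partly Complied.

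**6. Bias from a Week 1 baseline.** The document gives no figure for the change in HbA1c after one week of CGM, so this bias cannot be computed.

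**The case against.** The strongest reply is that a pre-CGM value exists for every eligible South African participant. Eligibility needs an HbA1c within 3 months, screening takes place at Day 1, and trial HbA1c results in South Africa are the routine ones. Partly Complied asks for a value recorded at Visit 1, which could be read as one available at that visit. A routine draw might also happen to fall on Day 1. All of this stands as a possible reading, but the article neither calls the eligibility value the baseline nor counts it as Visit 1.

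Second, Fully Complied is also named for the primary analysis and needs no Visit 1 value. That stands too. A reader might infer that no South African participant can be analysed, or that three of six clinics drop out of the primary analysis. The document does not support that: it would follow only for Partly Complied, and only on the strictest reading.

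Third, a reader might take 49% as the trial's power, or infer that a Week 1 baseline biases the result against CGM by a known amount. Neither is supported. The 49% rests on one assumed split and on excluding every South African participant, and the document gives neither size nor direction for a one-week effect. Nor would a Week 1 baseline cost Partly Complied its early drop-outs, because they lack Visit 5 anyway.

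Fourth, this may be one misplaced cell in a condensed article, and the South African protocols are not shown. Even so, the published passages conflict and need correcting.

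**Conclusion.** The concern holds as an internal contradiction about the baseline of the primary endpoint. Table 2 cannot be followed together with both the pre-CGM baseline and the Visit 1 requirement of Partly Complied, unless an unstated rule counts an earlier routine value as Visit 1. The population definition is the firmer problem, since it affects one of the two primary-analysis sets and the only set for hospitalisations. The bias from using Week 1 is probably small and cannot be quantified here.

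The fall in power from 80% to about 62%, 49% or 34% illustrates only what a literal exclusion would cost. It assumes that 246 covers both countries, that the South African share is 1/3, 1/2 or 2/3, and that 0.2 is Cohen's f. It is not an estimate of the trial's power. The point should still be settled before analysis, because it concerns the primary endpoint and the remedy is cheap.

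**What to change.** Reconcile Table 2 with the primary outcome and the population definitions:

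1. Define baseline in both countries as the last HbA1c before sensor application (for Arm 3, before the corresponding point on Day 1), within a stated window. For South Africa this may be the routine value within 3 months that eligibility already requires.
2. Reword Partly Complied as a baseline HbA1c and a Visit 5 HbA1c.
3. Where a routine draw can be taken on Day 1 before the sensor is applied, correct Table 2 to show it.
4. Fix the rule before any analysis, let it cover those already enrolled, and add a sensitivity analysis that uses the Week 1 value as the South African baseline.

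**Cost.** Items 1, 2 and 4 are changes of wording. Item 3 may not be possible everywhere. A reader might suppose that the draw simply moves by a week with no extra test, but specimens are taken only as part of standard care (section {33}), Table 2 puts the doctor's visit at Week 1 rather than Day 1, and South African recruitment began in September 2023 and January 2024.

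**Downside.** The eligibility value was selected to be at least 10%, so change within each arm will include regression to the mean. That matters for the within-group differences that Sample size {14} also claims to detect. The randomised comparison between arms is protected. Baseline would also be older in South Africa than in Kenya, where Day 1 is scheduled, and the report should say so.

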#### Primary outcome

Between-group analyses of the primary outcome will be conducted using the Fully Complied or Partly Complied populations and two-way repeated-measures ANOVA with time and arm as independent variables.

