### Trial design {8}

This trial is a pragmatic, parallel-group, open-label, multicentre, three-arm, superiority randomised (1:1:1) controlled trials of continuous or periodic CGM device use (the Abbott Freestyle Libre 1 device) versus standard of care in people with T1D in Kenya and South Africa. The primary endpoint is the mean change in HbA1c levels. The trial was designed using the PRECIS-2 tool, a nine-domain tool intended to be used in the trial design phase, which is intended to align design decisions with applicability of trial results [16]. 

The trial is expected to take approximately 18 months to complete (September 2023 to April 2025 in South Africa, and February 2024 to July 2025 in Kenya), including trial set-up, recruitment, and follow-up for all participants.

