### Criteria for discontinuing or modifying allocated interventions {11b}

A participant may discontinue CGM device use and be withdrawn for safety or administrative reasons at any time at the discretion of the Investigator. A participant may also decide to withdraw from the trial at any time. If a participant becomes pregnant, they will be permitted to remain in the trial to ensure external validity of the data.

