## Assignment of interventions: blinding

### Who will be blinded {17a}

As pragmatic, open-label trial, no blinding will be required.

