### Methods in analysis to handle protocol non-adherence and any statistical methods to handle missing data {20c}

Every effort will be made to collect full follow-up data for all participants, so it is expected that missing data will be minimal. Procedures to account for protocol non-adherence and missing, unused, or spurious data will be detailed in separate Statistical Analysis Plans, which will be developed and finalised before any analyses are performed.

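### The primary superiority comparison is fixed in two populations selected after randomisation, with no rule for choosing between them and no all-assigned efficacy analysis

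*Protocol article*

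**What the plan says.** Trial design {8} in the Protocol article describes a pragmatic, open-label study, one of "three-arm, superiority randomised (1:1:1) controlled trials". Under Who will be blinded {17a}, "no blinding will be required".

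Statistical methods {20a} then defines six populations. Four matter here:

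- Fully Complied: "Fully Complied: all participants who fully complied with the protocol".
- Partly Complied: participants with HbA1c recorded at Visit 1 and Visit 5 (Month 9) as a minimum.
- Assigned: "Assigned population: all participants who have been assigned to a trial arm and completed all Day 1 trial visit procedures".
- Safety: everyone assigned to an arm, with no further condition.

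For the primary outcome the same section says: "Between-group analyses of the primary outcome will be conducted using the Fully Complied or Partly Complied populations", using two-way repeated-measures ANOVA. The HRQoL and GMSS comparisons and the cost surveys use the same pair of sets, and hospitalisations use Partly Complied. Neither the Assigned nor the Safety set is attached to any efficacy analysis.

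Section {20c} leaves procedures for non-adherence and missing data to the SAP, and says that "it is expected that missing data will be minimal".

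**The concern.** Randomisation makes the arms comparable as assigned. Once participants are kept or dropped on what they did afterwards, that comparability is no longer guaranteed, and a difference between arms may reflect who remained and not what CGM did. For a superiority claim this is the wrong primary set.

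The wording between the two sets compounds the problem. It does not say which one carries the primary result, and nothing in the article prevents that choice from being made when arm-level results are already visible.

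The question answered is also at stake. The article sets out to inform policy on CGM within routine clinic care. That calls for the effect of assigning people to CGM, including those who wear it poorly or stop. A contrast among compliers does not estimate this.

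**Working it through.** **1. Are the sets post-randomisation?** Yes, both. Full compliance can be known only at the end of the schedule, and the Visit 5 HbA1c falls at Month 9.

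**2. Is selection the same in each arm?**

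- Fully Complied: under Intervention description {11a}, the continuous arm wears the device throughout 9 months with 2-weekly replacement, and the periodic arm wears it for 2 weeks around clinic visits. Under {6b}, Arm 3 receives standard of care, with no device. The visits, education sessions and most surveys are common to all arms, so compliance carries an added condition in the CGM arms.
- Partly Complied: the HbA1c criterion is identical in all three arms. Any imbalance would have to come from differential dropout, about which the documents say nothing.

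**3. How large could the bias be for Fully Complied?** The documents give no compliance rate, no correlation and no SD, so every input here is an assumption. Suppose a fraction p of an arm complies, compliance propensity and HbA1c improvement are jointly normal with correlation r, and the true effect is zero. The mean improvement among compliers is then r × SD × φ(c)/p, where c is the normal cut-off exceeded with probability p. The false benefit is

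r × SD × [φ(c₁)/p₁ − φ(c₀)/p₀], with 1 = CGM and 0 = control.

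| p₁ v p₀ | bracket | r | SD | false benefit (HbA1c points) |
|---|---|---|---|---|
| equal rates | 0 | any | any | 0 |
| any | any | 0 | any | 0 |
| 0.80 v 0.90 | 0.155 | 0.2 | 1.5 | 0.05 |
| 0.60 v 0.90 | 0.644 − 0.195 = 0.449 | 0.3 | 2.0 | 0.27 |
| 0.50 v 0.90 | 0.603 | 0.4 | 2.0 | 0.48 |
| 0.90 v 0.60 | −0.449 | 0.3 | 2.0 | −0.27 |

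The last row shows that the sign reverses if controls are the ones lost. This is why no direction can be given for Partly Complied.

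Two yardsticks from the article: Sample size {14} assumes a 2% change in HbA1c, and read as 2 HbA1c points this makes 0.27 / 2 = 13.5% of it. The review cited in {6a} gives pooled differences of 0.17 and 0.23, and 0.27 exceeds both.

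**4. Effect on the type I error.** A null simulation (4,000 runs, 82 per arm, one-way F test at 5%, both CGM arms excluded at the same rate) gave:

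| Excluded, CGM v control | r = 0 | r = 0.2 | r = 0.3 | r = 0.5 |
|---|---|---|---|---|
| 30% v 30% | 5.9% | 5.3% | 5.1% | 5.1% |
| 30% v 10% | 5.1% | 6.6% | 8.1% | 13.5% |
| 50% v 10% | 4.7% | 9.4% | 15.5% | 40.1% |

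The error stays near 5% when exclusion is equal or unrelated to outcome, and rises only when both conditions fail.

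**5. Effect on precision.** The plan's 246 reproduces as a one-way, three-group ANOVA with f = 0.2 and α = 0.05: the noncentrality is 246 × 0.2² = 9.84, and power is 80.4%. It contains no allowance for exclusions. On that same calculation, with assumed exclusion rates:

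- 10% excluded: N = 221, power 75.7%
- 20% excluded: N = 197, power 70.3%
- 30% excluded: N = 172, power 63.9%

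**The case against.** The strongest defence is that this is a condensed article and that non-adherence and missing-data handling are left to the SAP. That stands for anything the article leaves open, such as the wear threshold that counts as full compliance. It does not reach the population itself, which the article states.

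Four stronger readings are tempting, and the documents do not support them:

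- **That both sets favour CGM.** Only Fully Complied has a device condition. Partly Complied is a completer set with one criterion for all arms, and in an open-label trial controls might drop out more.
- **That bias of 0.27 points is established, or is as large as the effect sought.** It rests wholly on assumed inputs, applies only to Fully Complied and can be zero. It exceeds the cited pooled effects but is a small part of the change that the trial plans for.
- **That the named ANOVA will discard anyone with a missed visit.** This depends on implementation and on missing-data rules that {20c} leaves to the SAP.
- **That stopping the device ends HbA1c collection.** Section {11b} says that "A participant may discontinue CGM device use and be withdrawn for safety or administrative reasons at any time", but not that someone who only stops the device leaves follow-up. Section {18b} describes contacting participants and rescheduling missed visits.

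It can also be said that the Day 1 condition in the Assigned set will remove few people, since allocation itself happens at enrolment. That is probably so. But Day 1 includes device application or distribution in Arms 1 and 2 only, so the condition is not neutral between arms and is easily dropped.

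**Conclusion.** The point holds. As written, the primary comparison of a superiority trial rests on sets formed after randomisation, the choice between them is open, and no all-assigned efficacy analysis is named. That follows from the text and needs no assumption.

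Stricter selection in the CGM arms is a likely consequence for Fully Complied only. The direction for Partly Complied is unknown. The size of bias cannot be derived from the documents: for Fully Complied, the assumed scenarios run from zero to 0.48 HbA1c points, with 0.27 as one illustration that depends on 60% v 90% compliance, a correlation of 0.3 and an SD of 2. Because the flaw sits in the primary analysis, it should be corrected before the SAP is finalised.

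**What to change.** In Statistical methods {20a}, Primary outcome, name a single primary population: all participants assigned to an arm, analysed in that arm. The existing Safety definition already says this. The Assigned definition would serve if its Day 1 completion condition were removed. Use all available HbA1c values, including those recorded after a participant stops the device, preferably in a likelihood-based repeated-measures model. The model is a preference; the change of population does not depend on it.

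Keep Fully Complied and Partly Complied as supportive analyses, labelled as such. Apply the same rule to the HRQoL, GMSS, hospitalisation and cost/ICER comparisons. State explicitly that HbA1c continues to be collected from participants who stop the device but remain in the trial.

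If Partly Complied is kept, reconcile its definition with Table 2: it requires an HbA1c at Visit 1, while the South African schedule shows the first one at Week 1 (Visit 2).

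The cost is a change of wording and model code, some effort to follow up participants who stop the device, and possibly a less favourable estimate. Missing HbA1c values will still reduce precision, and the model will still rest on an assumption about why they are missing.

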### Participant timelines {13}

The duration for each participant will be 15 months, consisting of 9 months of intervention followed by 6 months’ follow-up. There will be six scheduled trial visits in total, at Day 1, Visit 2 (Week 1), and at 3 (Week 11/12), 6 (Week 23/24), 9 (Week 35/36), and 15 months (Week 57/58); Fig. 1).

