**ASSESSMENTS**							
Doctors visit (medical chart review)			All	All	All	All	All
HbA1c assessment		All		All	All	All	All
Medical events and resources survey				All	All	All	All
GMSS		All		All	All	All	All
HRQoL assessments		All		All	All	All	All
DDS		All		All	All	All	All
Acceptability questionnaire				Arms 1 and 2	Arms 1 and 2	Arms 1 and 2	
Focus group discussion^c^						All	

*CGM* Continuous glucose monitoring, *DDS* Diabetes distress score, *GMSS* Glucose Monitoring Satisfaction Survey, *HRQoL* Health Related Quality of Life

^a^Includes identification of potential participants to be invited to the screening and enrolment day

^b^In the continuous CGM arm, the device is applied once on Day 1 and used until Month 9, for the periodic arm, a new device is provided at the visits shown and used for 1 week before each clinic visit (except for the enrolment visit), and for 1 week after each clinic visit (except for the final follow-up visit)

^c^Performed in a subset of participants

**Table 2 Tab2:** Schedule of assessments (South Africa study; NCT05944718)

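### The Partly Complied set admits participants with HbA1c gaps whom a classical repeated-measures ANOVA running to Month 15 would drop

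*Protocol article*

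**What the plan says.** All references are to the protocol article.

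- **Analysis set.** Statistical methods {20a} defines Partly Complied by "all participants who recorded HbA1c values at Visit 1 and 5 (at least"). Values at Months 3, 6 and 15 are not required.
- **Method.** The Primary outcome paragraph of the same section compares arms, in either the Fully or the Partly Complied population, by "two-way repeated-measures ANOVA with time and arm as independent variables". The levels of time are not listed.
- **Endpoint.** Outcomes {12} defines it as the "mean change from baseline (pre-CGM device use) HbA1c at various timepoints up to 15 months".
- **Schedule.** Participant timelines {13} says "There will be six scheduled trial visits in total", with nine months of intervention and six of follow-up. The row "HbA1c assessment" has five entries in each country: Day 1 and Months 3, 6, 9 and 15 in Kenya (Table 1), and Week 1 and the same four months in South Africa (Table 2).
- **Missing data.** Section {20c} leaves procedures to separate analysis plans and says of full follow-up, "so it is expected that missing data will be minimal".
- **Other outcomes.** HRQoL gets the same two-way repeated-measures ANOVA. Between-group GMSS gets a two-way or one-way version, depending on which data are available.

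**The concern.** Partly Complied is built to tolerate gaps: two HbA1c values are enough to belong. A classical repeated-measures ANOVA, with time as the within-person factor, does not tolerate them, because it needs a value at every level of time for each person. Run over the five scheduled measurements, it would discard members whom the definition deliberately lets in.

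The Month 15 visit shows this best, since it falls six months after the intervention ends. A participant with HbA1c at baseline and Months 3, 6 and 9 who misses only Month 15 belongs to the set but contributes nothing, not even the end-of-intervention value. The people analysed would then be those who attended for all five measurements over 15 months. Attendance happens after randomisation and may differ between arms in an open-label trial, so this is a further selection that the name of the set does not reveal.

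**Working it through.** **1. The plan's own figure.** Sample size {14} gives 246 participants (82 per arm), effect size 0.2, 80% power and 5% significance. Reading 0.2 as Cohen's f in a three-group, single-timepoint ANOVA:

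- noncentrality = N × f² = 246 × 0.04 = 9.84, on 2 and 243 degrees of freedom
- power = 80.4%; at N = 243 it is 79.8%

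So 246 is the smallest balanced total reaching 80% on that basis. The section states no allowance for losses.

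**2. How many complete rows remain.** The article gives no missingness rate, so the rate p is an assumption. Take all 246 as members of Partly Complied (baseline and Month 9 present), with missingness p at each of Months 3, 6 and 15, independent between visits. Complete rows = 246 × (1 − p)³.

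| p per visit | (1 − p)³ | Complete rows |
|---|---|---|
| 5% | 0.857 | 211 |
| 10% | 0.729 | 179 |
| 15% | 0.614 | 151 |

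If the same people missed all three visits, the count would be 246 × (1 − p), or 234, 221 and 209. Clustered gaps therefore cost fewer participants than the table shows.

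**3. A simulated data set.** With 246 participants and 10% missing at each of the three visits, 178 had complete rows. A standard repeated-measures ANOVA routine with time as the within-person factor rejected the incomplete data as unbalanced. A mixed model with arm, time and their interaction used all 246 participants and 1154 values. Of 246 × 5 = 1230 possible values, 1230 − 1154 = 76 were missing. Restricting to complete rows would keep 178 × 5 = 890 values and so discard 1154 − 890 = 264 recorded ones, including 246 − 178 = 68 Month 9 values.

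**4. What this does to power.** On the single-timepoint basis of step 1, samples of 211, 179 and 151 give 74%, 66% and 58%. That basis has one outcome per person, so it does not describe the repeated-measures test in which the rows are lost. For the between-arm effect averaged over m = 5 measurements with within-person correlation ρ (assumed), noncentrality = N × f² × m / (1 + (m − 1)ρ). For example, N = 211 and ρ = 0.5 gives 211 × 0.04 × 5 / 3 = 14.07.

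| ρ | N = 211 | N = 179 | N = 151 |
|---|---|---|---|
| 0.3 | 98% | 96% | 92% |
| 0.5 | 93% | 88% | 81% |
| 0.7 | 85% | 78% | 71% |

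Power stays above 80% in seven of the nine cells. It falls below only at ρ = 0.7 with 10% or 15% missing per visit.

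**The case against.** The strongest reply is that the article fixes neither premise. It does not list the levels of time, and it does not say that incomplete participants are removed. If time meant only Visits 1 and 5, baseline and end of intervention, every Partly Complied member could be analysed. The article calls its statistical section an outline and defers missing-data procedures to an analysis plan that is not shown. Imputation there would keep incomplete participants without changing the named model. This stands, and it is why the point is conditional. The absence of a missing-data rule is not itself a finding.

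It does not remove the mismatch. The named method is already fixed, and the endpoint runs to Month 15, so limiting time to two visits would leave the later part of the endpoint outside the model. The expectation of little missing data does not help either, because the set was defined to admit gaps.

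A reader might infer three stronger things that the document does not support:

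- **That members with a gap cannot be analysed at all.** This holds only for a classical fit over all five measurements. HbA1c is also not scheduled at all six visits.
- **That the stated 80% power is lost.** The single-timepoint figures suggest it, but the repeated-measures figures mostly do not.
- **That GMSS is bound to the same model.** The article allows a one-way ANOVA there, so the point reaches only repeated GMSS scores.

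**Conclusion.** The point holds in conditional form. The Partly Complied definition and a two-way repeated-measures ANOVA to Month 15 do not fit each other unless the time factor is restricted or the method accepts incomplete rows. With five levels of time and a classical fit, a loss of roughly 14%, 27% or 39% of the set follows from 5%, 10% or 15% independent missingness at each of the three visits. These rates are assumptions, and clustered gaps would lose fewer people. The certain costs under those conditions are discarded valid values and a further selection after randomisation. Any loss of power depends on the within-person correlation and the effect tested, and no shortfall against 80% is claimed.

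**What to change.** In the Primary outcome paragraph of Statistical methods {20a}, and in the Secondary outcomes paragraph for HRQoL and repeated GMSS scores, replace the repeated-measures ANOVA with a likelihood-based mixed model for repeated measures. Use arm, visit and arm-by-visit as fixed effects with an unstructured within-person covariance, and include every available value. State which visits form the time factor. That statement should also say which measurement serves as the South African baseline, since Table 2 shows HbA1c at Week 1 and none at Visit 1.

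The cost is a wording change in two paragraphs and the matching text of the analysis plan, with standard software and no new data. The small downside is reliance on data being missing at random, which is a weaker assumption than a complete-case ANOVA generally needs. Whether Visit 5 should remain a condition for being analysed is a separate question about the analysis set, and this change does not settle it.
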